The researcher will select and randomly assign the samples to two intervention groups and one routine care group according to the study entry criteria. Eligible people are placed in one of three groups A: 36 people, B: 36 people, and C: 36 people, using permuted block randomization and open label. 18 blocks of 6 will be produced to create a sequence of size 108. In order to keep the random allocation list secret, a special code will be assigned to each of the intervention groups, which only the main implementer of the project will be aware of. Also, the second moderator, who is a student and study evaluator, and the person who performs the statistical analysis, will not know about the codes assigned to the drugs. The intervention group consisted of two groups of mothers, one group will receive black seed and olive oil and the other group will receive olive oil alone. To prepare the product, cold-pressed black seed oil is used, as well as standard extra-virgin olive oil (according to the national standard). Standard extra virgin olive oil is prepared by a company with pharmaceutical grade (Pisgaman Chemi). Cold-pressed black seed oil is obtained from pharmaceutical company (Barij Essential Oil). Both oils are mixed in equal proportions and packaged (29). Both products have approved specifications in terms of microbial and pollution control standards, chemical and physical control. The process of mixing and packaging of two oils is done under hygienic conditions in the traditional pharmacy laboratory of the Faculty of Traditional Medicine. All study subjects will be educated on following post-delivery health tips and caring for episiotomy wounds. The intervention groups (one group receiving olive oil plus black seed oil and the other receiving olive oil alone) will also receive instructions on how to use the containers containing the oils. Women in the intervention groups will use the oils 24 hours after delivery, applying 10 drops topically 3 times a day for 10 days (12). The participants will be instructed to wash and dry their perineum before applying the oils. They should then wear gloves and slowly apply 10 drops of oil to the perineum, massaging it in with their hands. The control group will receive only routine care. The researcher also examines the severity of perineal pain and episiotomy wound healing in both groups, the first 24 hours after delivery and ten days after that. Given that each milliliter contains 15 drops, and mothers are required to use the oils 3 times a day, approximately 30 mL of each type of oil will be provided to mothers for the duration of 10 days. To measure the intensity of episiotomy pain, a 10-cm pain ruler scale (6, 12) will be used, the zero mark of which means no pain and the mark of 10 is the worst possible pain. Episiotomy wound healing will be assessed by the researcher using the Rida scale (6, 12, 17). In this way, the participant will be placed in a lithotomy position and the variables of redness, edema, ecchymosis, discharge and approximation between the two edges of the episiotomy wound will be scored based on the REEDA scale (12).

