
Secondary outcomes include the monitoring of symptoms such as burning and itching, as well as the occurrence of episiotomy opening and the need for painkillers. These secondary outcomes will be assessed through a combination of examinations conducted by the researcher and self-reports provided by the mothers. Additionally, any side effects reported by each participant will be carefully reviewed, and the total number of side effects within each group will be documented.

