**Data collection tools**

The data collection tool will be Demographic Characteristics Questionnaire, REEDA scale and Visual Analog Scale.

**Demographic Characteristics Questionnaire:** This questionnaire comprises 22 questions that gather information such as age, education level, place of residence, employment status, height, weight, number of pregnancies and abortions, duration of hospitalization during labor, receipt of antibiotics during labor and post-delivery, and hospitalization of the baby in the intensive care unit. The questionnaire was designed based on the research objectives to identify potential confounding variables.

**Visual Analog Scale for Measuring Episiotomy Pain Intensity:** The Visual Analog Scale, also known as the McGill Pain Ruler, is a linear scale used for pain assessment. It consists of a 10-cm ruler, with 0 indicating no pain and 10 indicating the most severe pain possible, and between these 2 endpoints, the scale is divided into 3 levels. Perineal pain intensity refers to the pain experienced by mothers in their perineal area and is self-reported before and after the intervention.

**The Redness, Edema, Ecchymosis, Discharge, and Approximation Scale:** The REEDA (Redness, Edema, Ecchymosis, Discharge, and Approximation) Scale is a standardized tool for assessing episiotomy wound healing, including variables such as swelling, bruising, discharge, redness, and the distance between the two edges of the episiotomy wound. Each of these variables is scored on a scale from 0 to 3. The researcher records the scores for each variable separately after observing and examining the patient both before and after the examination. The overall score on the scale ranges from 0 to 15, with higher scores indicating less favorable wound healing and lower scores indicating better wound healing.

**Secondary outcomes assessment checklist:** Secondary outcomes will be determined by a checklist that will be completed by mothers on a daily basis during the first ten days after delivery and will be examined by the researcher.

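### The trial is open label although mothers rate their own pain; masking them to which of the two coded oils they receive would cheaply reduce expectation bias in the oil-versus-oil contrast

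*Protocol*

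**What the plan says.** In the Protocol, section Data Collection and Management, women are allocated to three arms "using permuted block randomization and open label". To protect the allocation list, "a special code will be assigned to each of the intervention groups, which only the main implementer of the project will be aware of". The section then names who is kept unaware: the student who acts as study evaluator, and "the person who performs the statistical analysis, will not know about the codes assigned to the drugs". Mothers are not named, and nowhere does the protocol describe look-alike containers or masking of participants.

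The two active arms are described thus: "one group will receive black seed and olive oil and the other group will receive olive oil alone". Their regimen is common, "applying 10 drops topically 3 times a day for 10 days", with the same instructions for washing, gloves and massage. On manufacture, the section says "The process of mixing and packaging of two oils is done under hygienic conditions" in the faculty's own laboratory. The third arm has routine care and no product.

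On who rates what:
- **Pain**, one of the two primary outcomes, "is self-reported before and after the intervention" (Data collection tools, Visual Analog Scale).
- **Secondary outcomes** (burning, itching, wound opening, painkiller need) rest on the researcher's examination together with "self-reports provided by the mothers", and on a checklist that mothers fill in daily for ten days.
- **Wound healing** (REEDA) is scored by the researcher.

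**The concern.** The masking protects the people who score the wound and analyse the data. It does not expressly protect the person who produces the pain score. A woman who knows that she has the combination the study is named for may report her pain differently from a woman who knows that she has the comparison oil. Any such reporting shift goes straight into the difference between the two oil arms. That contrast matters because the first specific objective compares pain across all three arms, and only combination versus olive oil alone shows what the black seed oil adds.

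The planned analysis cannot repair this. The ANCOVA adjusts for a measurement taken before the intervention, whereas the shift arises afterwards. The covariates in the multilevel regression do not help either, because knowledge of the oil coincides with the arm.

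Open label is unavoidable against a no-product arm. The protocol gives no reason why it must also cover one oil against the other.

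**Working it through.** **1. The protocol's own sample size.** Inputs from Sample size: SDs 1.5 and 2.2, means 5 and 6.4 (difference 1.4), 95% confidence, 80% power.

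n = (1.96 + 0.8416)² × (1.5² + 2.2²) / 1.4² = 7.849 × 7.09 / 1.96 = 28.39, so 29 per arm.

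The stated 36 per arm allows for a dropout rate that is not given. 1 − 29/36 = 19.4% and 1 − 28.39/36 = 21.1%, so about 20% is implied. The stated size reproduces, and masking would not change it.

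**2. Standard error of the oil-versus-oil pain difference at 29 evaluable women per arm.**

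SE = √((1.5² + 2.2²)/29) = √(7.09/29) = 0.494 cm.

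This borrows the SDs used for the sample size, which come from a cream study and not from a comparison of these two oils.

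**3. Effect of an assumed expectation shift.** Suppose there is no true difference between the oils and reporting shifts the contrast by b. The two-sided rejection probability at the 5% level is Φ(b/SE − 1.96) + Φ(−b/SE − 1.96).

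| Assumed shift b (cm) | Share of planned 1.4 | b/SE | False-positive rate |
|---|---|---|---|
| 0 | 0% | 0 | 5.0% |
| 0.3 | 21% | 0.61 | 9.3% |
| 0.5 | 36% | 1.01 | 17.3% |
| 0.7 | 50% | 1.42 | 29.4% |

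The values of b are assumptions; no figure in the protocol bears on them. The two-sided rate is the same whichever oil the shift favours.

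**4. Sensitivity to precision.** With all 36 per arm, SE = √(7.09/36) = 0.444, and a 0.5 cm shift gives 20.3% instead of 17.3%. Greater precision, from more women or from baseline adjustment, does not dilute a fixed bias; it makes the bias larger relative to the standard error.

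**5. Is masking between the oils feasible?** Drops, frequency, duration and technique are the same in both oil arms. Codes already exist, and the combination is mixed and packaged in-house. Two things are not stated: who fills the olive-oil-alone containers, and whether the two products look or smell alike.

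**The case against.** **Mothers may already be masked.** If only the main implementer knows the codes, that literally excludes mothers, and open label could refer just to the visible absence of a product in the routine-care arm. This reading is possible but does not displace the stated open label. The sentence about codes concerns secrecy of the allocation list, those kept unaware are then named without the mothers, and no look-alike containers are described. What stands is that the protocol never says outright that mothers are told their oil. The masking statement is unclear and needs reconciling on either reading.

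**Identical bottles may not mask.** This stands in part. Each woman handles the oil 3 × 10 = 30 times, and half of the combination is black seed oil. A reader might infer that coded identical bottles would largely remove the bias. The documents do not support that, because they are silent on smell and colour. The supportable claim is that the bias could be reduced.

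**The bias may be small.** This stands as to size. The protocol presents olive oil as beneficial too, so the gap in expectation between two promoted oils could be slight. A reader might take 9–29% as the trial's actual error rate, or assume that the shift must favour the combination. Neither follows: size and direction are both assumed, and the calculation is an unadjusted two-arm comparison, not the planned ANCOVA.

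**The scope is narrow.** True. The point bears on mother-reported outcomes in one of three pairwise contrasts. It does not concern the researcher-scored REEDA, and it leaves the comparisons with routine care as open as before.

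**Conclusion.** The point holds in a limited form. As written, the trial is open label, the codes are expressly withheld only from the evaluator and the analyst, and the mother alone rates a primary outcome. The combination-versus-olive-oil contrast is thus exposed to expectation bias that could be lowered at little cost and that analysis cannot correct afterwards.

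The size of the problem in this trial is unknown. Under the protocol's SDs, 29 per arm, no true difference and an assumed shift of 0.3 to 0.7 cm, the false-positive rate would rise from 5% to about 9–29%. That shows sensitivity, not measured harm.

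This is a change the sponsor should make, and it belongs in the protocol because masking has to be settled before women are enrolled. The sample size of 36 per arm is unaffected.

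**What to change.** - **Masking statement.** In Data Collection and Management, reconcile open label with the secret codes. Suggested sense: the trial is open label for oil versus routine care; mothers in the two oil arms are not told which oil they receive; the evaluator and the analyst do not know the codes.
- **Supply.** Provide both oils in identical opaque containers labelled only with the code, and state who fills each product.
- **Participant information.** Align it with this, so that women know they may receive one of two oils. Its present wording was not available for this review.
- **Check on masking.** After the day-10 pain score is recorded, ask each oil user to guess her oil, and report the answers by arm.
- **Reporting.** State that masking may have been partial, and that the contrasts with routine care were open for self-reported outcomes.

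The cost is matched containers, a change to the participant information and one extra question. Product, regimen, sample size and analysis model stay as they are. The main downside is that masking may be incomplete if the oils differ in smell or colour; the guess question makes that visible but does not cure it.

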### Data Collection and Management

This research will be conducted after obtaining permission from the Ethics Committee of Babol University of Medical Sciences, registering with the Iranian Registry of Clinical Trials, and obtaining the necessary sampling permits. After contacting the midwifery department of the hospitals affiliated with Babol University of Medical Sciences, the researcher invites eligible women to participate in the study. The researcher will first explain the study's purpose and the nature of the intervention to the women. The researcher ensures the confidentiality of their information, clarifies her responsibility for any treatment complications, and assures them that the treatment interventions will not change if they choose not to participate. Then, by obtaining the informed consent of the qualified, she will conduct convenience sampling.

Entry criteria for this study: primiparous women, natural vaginal delivery with episiotomy, literacy, and BMI < 30.

Exclusion criteria from this study: unwillingness of participants to continue participating in the study, fourth-degree tear, history of dermatitis, history of allergy and eczema diagnosed related to plants, and history of gestational diabetes and overt diabetes.

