**Possible implementation problems**

Not using sterile tape and using eye examination.

Some mothers may not come for examination on the 10th day. (For example, due to hospitalization of the baby)

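### The drug codes cannot mask oil versus routine care, and the protocol does not establish that whoever scores REEDA, a primary outcome, is unaware of the arm

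*Protocol*

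**What the plan says.** All of the following is in the Protocol.

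- **Masking.** Data Collection and Management describes allocation "using permuted block randomization and open label". The same paragraph says that only the main implementer knows the codes given to the intervention groups, and that they are withheld from the analyst and from "the second moderator, who is a student and study evaluator".
- **Recruitment and assignment.** In the same section: "The researcher will first explain the study's purpose and the nature of the intervention to the women", and "The researcher will select and randomly assign the samples to two intervention groups and one routine care group".
- **Outcome assessment.** In the same section: "The researcher also examines the severity of perineal pain and episiotomy wound healing in both groups", at the first 24 hours and again ten days later, and "Episiotomy wound healing will be assessed by the researcher using the Rida scale". Data collection tools adds: "The researcher records the scores for each variable separately after observing and examining the patient both before and after the examination".
- **Control arm.** Routine care only, with no oil, container or placebo.
- **Status of the outcomes.** The Primary outcome section names both pain intensity and wound healing. Pain is self-reported; REEDA is five items scored 0 to 3 by an observer, for a total of 0 to 15.

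The protocol does not say whether the researcher, the main implementer and the student evaluator are two people or three.

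**The concern.** Open label and an evaluator unaware of the codes are two different masking claims, and the protocol does not reconcile them. The safeguard it does describe, product codes, has nothing to act on in the routine-care arm. If the person who assigns a woman also scores her wound, that person knows whether she was given oil.

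REEDA rests on an observer's judgement, so knowledge of the arm can move the score. Statistical analysis plans ANCOVA on the pre-intervention measurement. Oil use starts 24 hours after delivery and baseline is scored within the first 24 hours, so expectation would act mainly on the day-10 score. Baseline adjustment cannot remove a day-10 drift that differs by arm, and nothing can repair it once the data are collected. Both comparisons of an oil with routine care are exposed.

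**Working it through.** **1. What the codes can hide**

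| Contrast | Can the codes mask it? |
|---|---|
| Combination vs olive oil alone | Possibly, if the two products cannot be told apart; the protocol does not say |
| Combination vs routine care | No: control has no product to code |
| Olive oil vs routine care | No, for the same reason |

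**2. Who the researcher could be**

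- *The main implementer.* She holds the codes, so the REEDA scorer knows the full allocation.
- *The student evaluator.* She does not hold the codes, but if she assigns women she learns who is in routine care. The scorer knows oil versus no oil.
- *A generic word for any team member.* The scorer may then be someone who did not assign. The text does not say so, and describes no measure that would keep the arm from whoever performs the examination.

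The first two readings give an unmasked scorer for oil versus routine care. The third leaves the matter open. All three need a change of text.

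**3. Sample size, to fix the arm size for the illustration**

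Inputs from Sample size: SDs 1.5 and 2.2, means 5 and 6.4, 95% confidence, 80% power.

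n = (1.960 + 0.842)² × (1.5² + 2.2²) / (5 − 6.4)² = 7.849 × 7.09 / 1.96 = 28.39, so 29 per arm.

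The protocol plans 36 per arm after an unstated dropout allowance; 1 − 29/36 = 19.4%. So 29 is roughly the number left if that allowance is used up, and 36 is the full arm.

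**4. What a scoring drift would do (illustration only)**

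The protocol gives no SD for REEDA. Assume an SD of 1.5 to 2.5 and a day-10 drift of 0.5 point in one arm. The standardised shift d is then 0.5/2.5 = 0.20, 0.5/2 = 0.25 or 0.5/1.5 = 0.33. With no true effect, a two-sided 5% two-sample t-test has non-centrality d / √(2/n), where √(2/29) = 0.2626 and √(2/36) = 0.2357.

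| d | Non-centrality, n = 29 | Rejection rate, n = 29 | Non-centrality, n = 36 | Rejection rate, n = 36 |
|---|---|---|---|---|
| 0.20 | 0.76 | 11.6% | 0.85 | 13.3% |
| 0.25 | 0.95 | 15.5% | 1.06 | 18.2% |
| 0.33 | 1.27 | 23.9% | 1.41 | 28.6% |

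The normal approximation agrees to within one percentage point. The nominal rate is 5%. Because the bias is fixed, the larger arm gives the higher false-positive rate. The table is for one oil-versus-routine comparison without baseline adjustment.

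**The case against.** The strongest objection is that the researcher is undefined. The protocol distinguishes a main implementer from a student whom it calls the study evaluator, and an open-label trial can still have a masked assessor. A reader might infer that the scorer certainly knows the arm. The documents do not establish that: it is the plain reading, not a proven fact. What stands is that the text contradicts itself on masking, and that its only described safeguard cannot reach the routine-care arm.

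Three further inferences should be resisted.

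- *That the daily checklist reveals the arm.* The Secondary outcomes section lists burning, itching, wound opening and need for painkillers. Nothing says the checklist records oil use, and women on routine care can report any of these. Keeping it from the scorer until REEDA is done is prudence, not the cure for a documented leak.
- *That visual scoring is part of the masking fault.* Possible implementation problems lists "Not using sterile tape and using eye examination". That is a measurement limitation the protocol discloses itself. A measured wound-edge gap would not make redness or discharge objective, and would mask nobody.
- *That the bias is known in size or direction.* Drift and SD are both assumed, and a smaller drift gives a smaller inflation. Bias towards the oils is the expected direction, not a certainty.

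A last objection concerns the remedy. Handing enrolment to the main implementer, who holds the codes, could trade assessment bias for selection bias, particularly with convenience sampling and fixed blocks of 6. That objection is sound, and the fix has to meet it.

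**Conclusion.** The point holds in limited form. The protocol's masking statements conflict. The codes can at most mask one of the three pairwise contrasts, and on the plain reading REEDA is scored by someone who knows oil versus routine care. This is a risk of bias on a primary outcome, not a demonstration of it.

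If the assumed drift of 0.20 to 0.33 SD occurred, the false-positive rate of a single oil-versus-routine test would be about 12-24% with 29 per arm and about 13-29% with 36. The textual conclusion does not depend on those figures.

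Masking the REEDA scorer would not protect the other primary outcome: pain is self-reported by women who know whether they are using an oil. The weakness should be corrected before recruitment, because the analysis cannot undo it.

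**What to change.** 1. **Scorer.** Name the student evaluator as the only REEDA scorer at both visits, with no part in enrolment, allocation or oil instruction. State who carries out those tasks.
2. **Order at the visit.** She scores REEDA before any discussion of care and before seeing the checklist. Women are asked not to reveal their group.
3. **Concealment.** Whoever enrols must not be able to foresee the next assignment. Because the main implementer holds the codes, reveal allocation only after consent and baseline scoring, for example by sequentially numbered, opaque, sealed envelopes. These are best prepared by someone who does not recruit.
4. **Wording.** Replace open label with a statement of who is masked to what: REEDA assessor masked to arm; self-reported pain unmasked against routine care; masking between the two oils claimed only if the coded products cannot be told apart.

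The cost is slightly more visit coordination and a one-off task of preparing envelopes. The main duties move between two roles the protocol already names. Masking will sometimes fail, for instance when a woman mentions her oil. Partial masking of the scorer is still better than none.
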